## Abstract

**Background:**

The prevalence of depression and anxiety has increased in recent years, with many individuals having trouble accessing mental health support. Smartphones have become an integral part of modern life, with apps offering new ways to deliver evidence-based self-help strategies to cope with common mental health symptoms. However, most of them do not have empirical evidence of their overall effectiveness or the effectiveness of their components, which could pose a risk for users.

**Objective:**

The aim of this study is to evaluate the effectiveness of the modules of evaluation, psychoeducation, and emotional regulation strategies in a multiplatform self-help mental health mobile app in the Maule region of Chile.

**Methods:**

A sample of 196 adults will be selected, who will be randomly assigned to different components of the app for a fixed period to assess its ability to reduce symptomatology.

**Results:**

The trial is not yet recruiting and is expected to end in October 2024. The first results are expected in April 2024.

**Conclusions:**

This is the first study in Chile to develop and test the effectiveness of a mobile app to manage anxiety and depression symptoms in adults. The intervention proposed is based on evidence suggesting that the internet or remote intervention tools and self-management of prevalent symptomatology could be the future of mental health care systems in the digital era. If the effects of the intervention are positive, wide implementation in Chile and other Spanish-speaking countries could be possible in the future.

**International Registered Report Identifier (IRRID):**

PRR1-10.2196/52324

## Introduction

### Background and Rationale

Mental health disorders are common in the general population. In Chile, depression and anxiety are the most frequently observed psychopathologies, with a prevalence of 5% for depression and 6.5% for any form of anxiety [1]. However, the population affected by depression or anxiety symptoms may be greater, with 49.2% of Chileans reporting some level of depression symptoms [2]. These prevalences have become a significant issue in public health settings, where waitlists in public mental health services in Chile are mostly stagnant [3], and in the past 2 years have become extensive due to the COVID-19 pandemic. Thus, it becomes necessary to find alternatives that allow providers to respond to this need for mental health access [4].

In this context, the use of remote self-guided psychological interventions, such as those found in mental health mobile apps, has gained popularity [5]. It has been reported that this remote modality improves access, reduces waiting times for appointments, saves time, and reduces the effect of attitudinal barriers in patients seeking psychological support [6]. Studies indicate a high effectiveness rate of web-based care, with smartphone-based psychological interventions reducing user anxiety [7] and depression [8,9]. Accordingly, there has been an increased number of mental health mobile apps available to users. However, many of them do not have sufficient theoretical support for their effectiveness. In 2015, a total of 447 apps related to cognitive behavioral therapy (CBT) were found available in any App Store [10]. Conversely, 9 studies regarding the use of smartphones in cognitive-behavioral interventions were found, of which only 2 had readily available apps in the market [10]. Moreover, 10% of those who say they use cognitive behavioral interventions as a theoretical basis were not evidence-based [11]. It has been suggested that, without empirical support, these apps can be potentially harmful to users [12].

Among the small portion of mobile apps that have empirical support for their tools, 3 specific components or modules have the highest rates of applicability and effectiveness for reducing depression and anxiety: assessment, education, and self-regulation digital tools [13]. The assessment component allows for the recognition of the current symptomatic state of the user, while the constant evaluation helps the monitoring and the development of awareness of the process of change in the symptomatology [14]. The psychoeducation process allows users to be informed about what they are experiencing. Although psychoeducation alone is an effective strategy for the improvement of some anxiety and depression symptoms [15,16], its effectiveness increases when it is accompanied by other strategies [17]. The final component, the use of self-regulation tools, demonstrates a series of brief, easy-to-use self-guided activities that attempt to regulate, express, or otherwise manage psychological distress, low mood, and symptoms of anxiety.

The presentation of these modules normally follows the theoretical framework of CBT. This treatment model can be easily adapted to non–face-to-face environments and has been repeatedly tested in web-based modalities [18,19]. Moreover, other approaches theoretically derived from CBT, such as behavioral activation therapy or mindfulness-based behavioral therapy, also exhibit evidence of their effectiveness in non–face-to-face settings [20]. The behavioral activation treatment for depression attempts to regulate depression symptoms through the programming of pleasurable activities [21], while mindfulness-based CBT focuses primarily on breathing techniques, relaxation, self-compassion, and mindfulness abilities [22], aimed at regulating anxiety states.

According to the literature, there are no mobile apps with scientific support to address depression and anxiety symptoms in the adult population in Chile. The regular and widespread use of such apps could help provide self-care tools to individuals who are reticent about therapy.

### Aims

The main aim of this study is to develop a multiplatform self-help mental health mobile app for adults and to test the effectiveness of its assessment, psychoeducation, and emotional regulation strategy modules post intervention and at 1-month follow-up. We hypothesize that the combination of psychoeducation and any self-regulatory strategies will prove more effective than the evaluation and psychoeducation components alone in decreasing symptomatology.

### Trial Design

This is a protocol for a double-blind, 4-armed randomized controlled trial (ClinicalTrials.gov NCT05997849) evaluating changes in primary and secondary outcomes (symptomatology and well-being variables) post intervention and at follow-up. The 4 arms will be group 1 (control): the participants will have access only to the monitoring and psychoeducation module for 30 days; group 2: participants will have access to the monitoring module, psychoeducation, and mindfulness strategies for 30 days; group 3: participants will have access to the monitoring module, psychoeducation, and behavioral activation strategies for 30 days; and group 4: participants will have access to the monitoring, psychoeducation, and cognitive strategies module for 30 days. Additionally, 1 focus group per condition will be carried out to qualitatively assess the user experience with the app and its overall usability.

## Methods

### Study Setting

Participants will be adults (18 years of age and older) in the Maule Region of Chile and mixed-sex. We expect to recruit 49 participants per arm, configuring 196 participants in total.

### Eligibility Criteria

Adult Chilean citizens, 18 years of age or older, with access to a computer, tablet, or smartphone (Android or iOS) with internet, and no untreated mental health diagnosis, will be included in the study. The mental health diagnosis and current treatment will be assessed solely by the participant’s self-report.

Individuals who self-report substance abuse problems or any current serious mental health disorder and participants reporting scores greater than 1 on question 9 (suicidal ideation) on the Patient Health Questionnaire–9 (PHQ-9) will be excluded from the study.

### Ethical Considerations

This study and all associated documents were approved by the Scientific Ethics Committee of the University of Talca (14/2022). Informed consent will be obtained from all participants through web-based forms before the allocation process begins. The collected data are completely deidentified and stored in secure servers (see Data Management section). Participants will not receive any type of compensation for their participation in the study.

### Recruitment and Informed Consent

For recruitment, invitations will be made through the social networks of the Center for Applied Psychology and the Faculty of Psychology of the University of Talca. In addition, the educational and health services of 4 districts in the region will be contacted to disseminate the multiplatform application Cuidandome to adults. The call for participation will include an explanatory video and an informed consent form, which will be available on and collected through the project website (under development). Participants will be recruited through convenience sampling and will be randomly assigned to 1 of the 4 groups by means of simple randomization (through the PHP: Hypertext Preprocessor rand() function).

### Interventions

#### Description of Interventions

Cuidandome is a multiplatform self-help mental health app that does not constitute a psychological treatment. The mobile app will be available for iOS and Android operating systems, and it is composed of 3 modules: monitoring, psychoeducation, and strategies for people to learn to manage their emotional states and their depression or anxiety symptoms.

The modules of the app are given below.

#### Monitoring (M) Module

The aim of this assessment module is to acquire information on the symptoms and well-being of the participants in the process of using the app and their satisfaction with the strategies. This transversal component is composed of a weekly assessment and a brief daily mood assessment so that the person can monitor their own mood.

#### Psychoeducation (P) Module

The aim of this module is to provide information to the user about different aspects of mental health care, understanding depression and anxiety symptoms, and the fundamentals of the app and how to get the most out of it. Several studies have shown the relevance of psychoeducation in mental health care.

#### Regulation Strategies (RS) Module

This module is based on cognitive behavioral change techniques and strategies originating from the basic principles of CBT for the treatment of depression and generalized anxiety, behavioral activation therapy for depression, and mindfulness strategies for managing anxiety and depression. The module is organized into 3 types of strategies: cognitive (strategies to help modify cognitions that cause discomfort), behavioral activation (strategies focused on modifying behavior that causes discomfort), and mindfulness (strategies to help stay in the present moment and decrease activation of the sympathetic nervous system). Each of the strategies will be developed sequentially through 3 tasks: understanding, learning, and practicing; providing activities to understand why the strategy works and how it should be done; and finally, putting the strategy into practice. Figure 1 shows the overview of the dashboards.

**Figure 1 figure1:**
[figure not shown]
Main dashboard (left) and regulation strategies: square breathing dashboard (right).

### Criteria for Discontinuing or Modifying Allocated Interventions

Participants in any group can leave the study at any time if they wish without any consequences; this means that their information and collected data will not be analyzed.

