### Sample Size

To achieve the aims of the study, we have considered 4 arms. To obtain a statistical power of 0.80, a minimum sample size of 36 participants is required for each of the 4 arms. Controlling for a dropout rate of 26%, as shown by the literature on behavioral experiments linked to mobile apps for symptoms related to mood and anxiety [32,33], a final sample size of 49 participants per group is required. The sample size approximation was made based on the literature on statistical power and sample sizes in clinical and social science research [34], while the estimate to reduce the effects of the percentage of abandonment in the experimental conditions was calculated based on Wang and Ji [33]. Thus, an estimate of 196 participants sufficiently obeys such parameters. In addition to the quantitative data collection, a qualitative collection of information will be carried out through focus groups. Regarding the number of focus groups, a total of 4 have been established, 1 for each study group. The size of the focus groups, following the recommendations in the literature [35], is estimated at a total of 32 participants (reaching an estimate of the saturation point), that is, 8 participants per focus group.

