### Statistical Methods

#### Statistical Methods for Primary and Secondary Outcomes

We will use descriptive statistics to assess balance across groups at baseline. The primary between-group analysis will be carried out on an intention-to-treat basis for GAD-7 and PHQ-9 scores. We will use a linear mixed model for repeated measures (MMRM) analyses to compare all the intervention and control groups regarding the change in all outcome measures from baseline to post intervention and at follow-up. All the models will be adjusted for sex, age, educational level, and concurrent psychological or psychiatric treatment. Analysis will be carried out with SPSS 26 (IBM Corp) and Stata 15.01 (StataCorp).

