#### Methods in Analysis to Handle Protocol Nonadherence and Any Statistical Methods to Handle Missing Data

Primary outcomes will be assessed using an intention-to-treat analysis. Missing data will be reduced to a minimum by (1) rendering it impossible to advance on the app if a questionnaire is not completed in full, and (2) using the appropriate measures to encourage participants to fill out the follow-up questionnaires. Multiple imputations will be used to handle any missing data in the analyses.

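### Excluding all data of participants who leave the study contradicts the stated intention-to-treat analysis with MMRM and multiple imputation

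*Protocol article*

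**What the plan says.** The Protocol article, under Criteria for Discontinuing or Modifying Allocated Interventions, states: "Participants in any group can leave the study at any time if they wish without any consequences". It then spells out the consequence: "this means that their information and collected data will not be analyzed". The rule applies to every arm and every time of leaving, and it covers data already collected. It is not limited to people who ask for their data to be withdrawn.

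Statistical Methods for Primary and Secondary Outcomes states: "The primary between-group analysis will be carried out on an intention-to-treat basis for GAD-7 and PHQ-9 scores". The model is given as: "We will use a linear mixed model for repeated measures (MMRM) analyses to compare all the intervention and control groups". The section on nonadherence and missing data repeats the principle, "Primary outcomes will be assessed using an intention-to-treat analysis", and adds: "Multiple imputations will be used to handle any missing data in the analyses".

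No section reconciles the exclusion rule with the intention-to-treat statements.

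**The concern.** Intention-to-treat keeps each randomised participant in the assigned arm. The withdrawal rule takes a leaver out altogether. The analyst has to break one of the two rules for every such person, and the article does not say which one governs.

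The exclusion also works against the chosen methods. MMRM and multiple imputation cope with dropout by using what the dropouts did provide. Here that is the baseline GAD-7 and PHQ-9, the weekly in-app assessments of the Monitoring module and, for later leavers, the post-intervention scores. The rule sets this information aside for the participants whose later outcomes are unknown.

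Leaving happens after randomisation. The control arm receives monitoring and psychoeducation only, while the other three arms add a strategy module, so leaving could differ by arm. If it does, and is also related to outcome, the comparison no longer rests on the randomised groups although it is labelled intention-to-treat.

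**Working it through.** **1. The plan's own figure.** From Sample Size: "To obtain a statistical power of 0.80, a minimum sample size of 36 participants is required for each of the 4 arms", with 26% dropout.
- 36 / (1 − 0.26) = 36 / 0.74 = 48.65, rounded up to 49 per arm.
- 49 × 4 = 196. The stated figure is reproduced.

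The base of 36 cannot be checked, since effect size and alpha are not given, but nothing below depends on it.

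**2. How many participants the rule can remove.**
- Upper limit, if every planned dropout counts as leaving: 196 × 0.26 = 50.96, about 51. That leaves 196 × 0.74 = 145.04, about 145 in total, and 49 × 0.74 = 36.3 per arm.
- Lower limit, if all dropouts merely fall silent and none leaves: 0.
- Under intention-to-treat, none of the 196 is removed.

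Even at the upper limit about 36 per arm remain, which is the number the plan wants for power. The issue is therefore who is compared, not the sample size.

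**3. Bias from excluding leavers.** The documents give no dropout by arm and no correlations, so these inputs are assumptions: true effect 0, correlation 0.6 between any two visits, and leaving correlated ±0.5 (or 0, where stated) with the score on a latent scale. Results come from simulation with 2,000,000 participants per arm, in SD units and absolute size. The direction reverses if the arms swap roles.

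*Leaving depends on the baseline score.* With equal rates and reasons the bias is about 0. Otherwise the unadjusted comparison of stayers is off by 0.09 SD (36% against 16% leaving), 0.13 SD (26% in each arm, related to severity in one arm only) and 0.26 SD (26% in each arm, opposite directions). Adjusting for the baseline score brings all three to about 0.00.

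*Leaving depends on the post-intervention score; contrast at follow-up.*

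| Pattern of leaving | Stayers only, baseline-adjusted | Leavers' observed scores kept, missing at random |
|---|---|---|
| 26% in each arm, same reasons | 0.00 | 0.00 |
| 36% against 16%, same reasons | 0.04 | 0.00 |
| 26% in each arm, score-related in one arm only | 0.05 | 0.00 |
| 26% in each arm, opposite directions | 0.11 | 0.00 |

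The last column is zero because leaving was made to depend only on a score that had been observed. If leaving depends on something the recorded scores do not predict, part of the bias stays even when the data are kept.

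**The case against.** The strongest defence reads leaving as active withdrawal. On that reading, people who stop using the app or skip questionnaires stay in the intention-to-treat set and are imputed, and only formal withdrawers are excluded. This is plausible: the app is self-guided, adherence is not monitored, and a participant can go silent without leaving. It narrows the conflict but does not end it. Formal withdrawers are still randomised participants, the exclusion still reaches data they had already given, and leaving is not defined. The rule also stands under a heading about discontinuing the intervention, which blurs stopping the app with leaving the study.

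A second defence is ethical: respecting a request that data not be used is legitimate. That stands, and the fix preserves it. Leaving a study is not in itself such a request.

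On size, the other side is largely right, and three stronger readings should be resisted.
- A reader might infer that about 51 participants are expected to be excluded. The 26% is a dropout rate taken from literature on app experiments, and the article does not equate it with leaving.
- A reader might multiply dropout by an assumed gap between leavers and stayers in the strategy arms only. With a gap of 0.3 to 0.8 SD this gives 0.26 × 0.3 = 0.08 to 0.26 × 0.8 = 0.21 SD. No section supports that one-sided pattern. The product is also total attrition bias, as if all outcomes could be known; the clause is responsible only for the part that retained data could recover.
- A reader might infer that data are erased. The text says only that they are not analysed.

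Nor do the documents show that leaving will differ by arm. Participants are not told their group, and the daily reminders are described without distinction by arm.

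**Conclusion.** The contradiction holds as written. It is not a detail left to a fuller document: the article states a rule that conflicts with its own primary analysis, and following that rule makes the analysis stayers-only as far as leavers are concerned. It does not follow that the whole primary analysis becomes a completers analysis, since participants who are silent but have not left may still be kept and imputed.

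The number affected lies between 0 and about 51 of 196. Bias is a risk and not a certainty, because it needs leaving to relate to outcome differently across arms. Under the assumed correlations and leaving rates it runs from about 0 to 0.04–0.11 SD at follow-up after baseline adjustment, and the top value needs 26% leaving in opposite directions by arm. The contradiction itself rests on none of these assumptions. It should be settled before recruitment, because a promise made to participants at consent would be hard to reverse later.

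**What to change.** Replace the exclusion clause with wording such as:

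> Participants may stop using the app, or stop answering, at any time. Data collected up to that point are kept and analysed in the randomised arm. Participants who only stop using the app are still invited to the post-intervention and follow-up questionnaires. Data are removed only if a participant explicitly revokes consent to their use, and the number of such removals is reported by arm.

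State that the MMRM and the imputation are run on all randomised participants except those removals.

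The consent text is not shown. If it repeats the exclusion promise, it must be changed to match. The ethics committee has already approved the study documents, so it should be notified under the article's own procedure for substantial amendments. The Results section says that recruitment has not begun, so this can be done before anyone consents.

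The cost is a small protocol and consent amendment. No extra participants are needed: the sample size stays at 49 per arm and 196 in total.

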### Outcomes

#### Primary Outcomes

Anxiety symptom is 1 of the 2 primary outcomes, and it will be measured by the Generalized Anxiety Disorder–7 Scale (GAD-7). It consists of 7 items that the person assesses on a scale of 0-3 according to the frequency with which each symptom has disturbed them during the past 2 weeks [23]. It shows high reliability in Chilean samples (Cronbach α=0.86 [24]).

Depression symptoms will be measured by the PHQ-9 depression scale, which consists of 9 items that evaluate the presence of depression symptoms present in the past 2 weeks, with a response scale of 0=never, 1=some days, 2=more than half the days, and 3=almost every day. With a Cronbach α of 0.83, its reliability is high in Chilean samples [25]. Additionally, depression and anxiety symptoms in the past week will be assessed through the Patient Health Questionnaire–4 (PHQ-4) [26].

Primary and secondary outcomes will be assessed at 3 time points: preintervention (baseline), immediately post intervention (30 days post intervention), and 1-month follow-up in all groups.

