#### Composition of the Data Monitoring Committee, Its Role, and Reporting Structure

A monitor from the Ethical Scientific Committee of the Universidad de Talca will check once a year the presence and completeness of the investigation. This committee is independent of the sponsor and has no competing interests. For further details, please contact [contact].

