#### Adverse Event Reporting and Harms

The intervention does not cause any harm to the participants. However, if participants experience emotional distress upon using the app, they can contact the lead investigator at any time, who can provide them with options for referral to other public mental health services available. This procedure is explained in detail in the informed consent and initial training videos.

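### The rule that the data of anyone who leaves will not be analysed contradicts the planned intention-to-treat analysis with multiple imputation

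*Protocol article*

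**What the plan says.** Three sections of the protocol article bear on this.

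- Criteria for Discontinuing or Modifying Allocated Interventions lets participants in every group leave whenever they choose, and adds: "this means that their information and collected data will not be analyzed". It does not separate stopping use of the app, stopping follow-up, and asking for data to be withdrawn.
- Statistical Methods for Primary and Secondary Outcomes states: "The primary between-group analysis will be carried out on an intention-to-treat basis for GAD-7 and PHQ-9 scores". The model is a linear mixed model for repeated measures on change from baseline to post intervention and follow-up, adjusted for sex, age, educational level and concurrent treatment.
- Methods in Analysis to Handle Protocol Nonadherence and Any Statistical Methods to Handle Missing Data repeats the intention-to-treat commitment and states: "Multiple imputations will be used to handle any missing data in the analyses".

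After baseline, the outcomes are measured "immediately post intervention (30 days post intervention), and 1-month follow-up in all groups". Sample Size plans for 26% dropout. No section reconciles the first statement with the other two.

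Separately, Adverse Event Reporting and Harms opens with: "The intervention does not cause any harm to the participants". Its next sentence provides for participants who become distressed when using the app.

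**The concern.** An intention-to-treat analysis keeps each randomised person in the arm to which they were allocated, whatever they do afterwards. A rule that deletes a person's record because they later chose to leave makes the analysed set depend on post-allocation behaviour, and that behaviour may be related to the symptoms being measured.

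The rule also throws away data that exist. A participant who completes the post-intervention questionnaires and leaves before the 1-month follow-up would lose a recorded PHQ-9 and GAD-7 score, although only the later score is truly missing. The mixed model and the imputation are there to make use of such partial records.

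At stake is the protection that randomisation gives to the primary comparison. The analyst would also have to break one written statement in order to keep another. The Discussion (Overview) itself names dropout as a threat to the results.

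**Working it through.** **1. Reproduce the plan's own figure.** Inputs from Sample Size: 36 per arm needed, 26% dropout, 4 arms.

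- 36 / (1 − 0.26) = 48.65, rounded up to 49 per arm.
- 4 × 49 = 196.

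Both agree with the article. The 36 cannot be checked because no effect size, standard deviation or alpha is given, but this point does not depend on it.

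**2. Upper bound on the number removed.** If every planned dropout were an active leaver:

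- per arm: 0.26 × 49 = 12.74, about 13;
- in total: 0.26 × 196 = 50.96, about 51;
- analysed: 196 − 51 = 145, about 36 per arm, instead of 196.

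**3. Below the upper bound.** The article does not say what share of dropout is active leaving. The shares below are assumptions.

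| Assumed share of dropout that is active leaving | Removed per arm | Removed in total |
|---|---|---|
| 10% | 0.10 × 12.74 = 1.3 | 5 |
| 25% | 0.25 × 12.74 = 3.2 | 13 |
| 50% | 0.50 × 12.74 = 6.4 | 25 |
| 100% | 12.7 | 51 |

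**4. Can the statements be reconciled?** One could try counting leavers as randomised and imputing all their outcomes. But the exclusion covers their information as well as their outcome data. On its plain wording, baseline scores and covariates go too, and the imputation would have nothing except the arm to work from. It would then fill in values resembling those who stayed in that arm, which carries no information about the leavers. This does not restore an intention-to-treat analysis in any useful sense.

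**5. How exclusion can bias the comparison.** Let d be the proportion of an arm that leaves and g the amount, in standard deviations, by which leavers do worse than stayers. The mean among stayers is then better than the mean of the whole arm by d × g. With the same g in two arms T and C, analysing stayers only shifts the contrast by (dT − dC) × g. The values below are assumed; each pair of rates averages 26%.

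- 32% v 20% leaving: 0.12 × 0.3 = 0.04 SD, up to 0.12 × 0.8 = 0.10 SD.
- 36% v 16% leaving: 0.20 × 0.3 = 0.06 SD, up to 0.20 × 0.8 = 0.16 SD.
- 26% v 26% with equal g: 0.

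The last line does not mean that a common leaving mechanism is harmless. Suppose that people with worse symptoms are more likely to leave, by the same rule in every arm. If a strategy truly works, the control arm has more people with worse symptoms, so it loses more of them. The proportions leaving, and who leaves, then differ because of the effect itself, and the estimate is distorted. Only under no true effect does an identical mechanism leave the contrast undisturbed.

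**The case against.** The best defence is that the sentence is withdrawal-rights language: it protects people who revoke consent, and excluding their data is then proper. The consent form and full protocol are not shown and may draw the distinction. Part of this stands. The rule concerns people who choose to leave, so for those who fall silent the intention-to-treat analysis with imputation works as written, and the number affected may be well below the upper bound. What does not stand is reading the sentence as limited to revoked consent: it sits under discontinuing the intervention, covers any participant who leaves, and makes no such distinction.

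A second objection is that the fix recovers little. This is partly right. For someone who leaves before the post-intervention assessment, the only scheduled PHQ-9 and GAD-7 scores may be those at baseline. The clear gain is in those who leave between the post-intervention assessment and follow-up.

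A reader might infer something stronger: that the rule hides distressed users from harms reporting, so that an arm could look safe because its distressed users are not counted. The pieces are suggestive. The article asserts in advance that there is no harm, the committee's monitor "will check once a year the presence and completeness of the investigation", and the in-app monitoring, "composed of a weekly assessment and a brief daily mood assessment", is given no stated safety role. But the article describes no harms analysis from which leavers could be removed. The contact and referral route for distress is untouched by the rule. How adverse events are collected and tabulated is what a condensed article may leave to the full protocol. That leavers are distressed is a possibility, not something the article shows.

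A reader might also infer a loss of power. That is not supported either: even at the upper bound about 36 per arm remain, which is the number the article says it needs for power of 0.80.

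**Conclusion.** The contradiction is real and stands in the current text. For participants who actively leave, the discontinuation rule and the intention-to-treat analysis with imputation cannot both be followed. The rule would also delete observed post-randomisation scores.

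The number affected is at most about 13 of 49 per arm (51 of 196). That bound assumes that the 26% dropout occurs as planned and consists wholly of active leaving; the true share is not given. Bias is possible if leaving is related to outcome, either because leaving differs by arm or, where there is a true effect, even with the same leaving mechanism everywhere. Its size and direction cannot be derived from the article; the 0.04 to 0.16 SD shown above rests entirely on assumed values.

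On harms, only a wording point survives: the article should not state as fact, before any data, that the app causes no harm, and then provide for distress from using it.

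**What to change.** 1. Replace the exclusion in Criteria for Discontinuing or Modifying Allocated Interventions, and put the same line in the consent form: *Data collected before a participant leaves will be kept and included in the intention-to-treat analysis unless the participant withdraws consent for their use.*
2. Report by arm the number who leave and the number who withdraw consent for use of their data.
3. As a minor edit, delete the opening no-harm sentence of Adverse Event Reporting and Harms and keep the contact and referral procedure.

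The cost is one changed sentence, one consent-form line notified to the ethics committee under the article's own amendment procedure, two counts per arm and one deletion. According to Results, the trial is not yet recruiting, so nobody should yet have been enrolled under the present rule. Later, using leavers' data might require fresh consent. Participants lose no right, since they can still have their data withdrawn. The limit of the change is that it will add little beyond baseline for those who leave before the post-intervention assessment.
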